# Study Enrollment and Withdrawal

Opioid treatment programs (OTPs) will be recruited to participate in this stepped wedge trial by State partners via email invitations, announcements via State listservs, and announcements at relevant meetings to contact the Project Manager or the Principal Investigators. A total of 36 programs will be recruited at the beginning of the trial (Year 2). The intervention is delivered to the leadership and staff members at the clinic-level. Zoom meetings will be conducted with directors of programs to confirm their enrollment and to explain the timeline and expectations. The Project Manager will monitor enrollment and if enough clinics do not enroll, additional enrollment techniques will be discussed with the study team and implemented. In order to retain clinics in the trial, the study Project Manager and the Facilitators will stay in regular contact with the clinic program director to ensure that any concerns are addressed and to answer any questions. If a clinic is considering withdrawing from the study, the Project Manager will schedule an in-person/online meeting to further discuss and try to address reasons for desired withdrawal. We expect that offering the intervention to clinics will be attractive because the intervention will offer training and external facilitation free of charge, which the study team has found in their experience in providing Statewide technical assistance is very welcome during the period of state reforms and COVID-19 Public Health Emergency; therefore, do not anticipate problems with enrollment. Any issues with clinic enrollment and retention that cannot be resolved by the Project Manager will be discussed with the Principal Investigators for resolution. In addition, recruitment and retention will be discussed during regular weekly study team meetings.

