## Duration of Study Participation

During year 1 of the study, we will draw potential sites from OTPs with high and low THD flexibility. We anticipate to recruit 10 OTPs (5 high and 5 low THD flexibility) on clinical and organizational factors affecting take-home dosing decisions based on our quantitative study during year 1. After the consent from the OTPs, we will recruit leadership (e.g., program director, clinical supervisor, etc.) and frontline treatment staff (e.g., addiction physicians, hospital nursing and social work leaders, hospitalists, administrative staff, etc.) for one-on-one interviews. Before the trial begins, clinics will be randomized into 6 cohorts of six-months long interventions over three years. Using large administrative data, we will be able to track clients within each OTP over four years, including a pre-intervention six-month baseline period. Six clinics in each cohort will receive the intervention for six months. In years 2-4, we plan to conduct a post-intervention survey with providers/staff and interviews with providers and patients. The qualitative research will include data from approximately 174 addiction treatment staff and 144 patients being interviewed about take-home dosing practice changes after the intervention has been implemented. Recruitment will end will end when either 174 staff and 144 patients are interviewed or saturation is reached.

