### Years 2-5

We propose an embedded mixed methods^[[173]](#endnote-173)^ study in which we will employ a stepped-wedged randomized controlled trial with 36 OTPs to test whether the intervention a) increases THD, b) increases retention in care, and c) has any effect on adverse events (i.e., emergency department visits, hospitalizations, mortality). OTPs will be randomized across 6 sequential steps between years 2 and 4. The examination of outcomes will benefit from access to rich sources of data described below. Qualitative data collection with staff and patients will be embedded within the trial to examine experiences with the new THD protocols and to inform quantitative findings. Based on analyses conducted during phase 1 of this project, we will recruit 36 OTP clinics from among the lower ranked OTPs based on client case-mix adjusted THD performance. Clinic recruitment will also be proportionate to the geographical distribution of OTPs across the State. In a current trial with similar approach (R61/33DA049252),^[[174]](#endnote-174)^ we have had strong success in recruiting and retaining 30 non-OTP outpatient clinics.

Before the trial begins, clinics will be randomized into 6 cohorts of six- month long interventions over three years.^[[175]](#endnote-175)^, ^[[176]](#endnote-176)^, ^[[177]](#endnote-177)^, ^[[178]](#endnote-178)^, ^[[179]](#endnote-179)^ Using large administrative data, we will be able to track clients within each OTP over four years, including a pre-intervention six-month baseline period. Six clinics in each cohort will receive the intervention for six months.

Client interviews (n=40) from participating OTPs will explore experiences related to THD, notably among Black/African American and Latinx clients. An interview guide will be created to reflect the dimensions of the HEIF. We will use maximum variation purposeful sampling by recruiting clients from participating OTPs in urban and rural locations as well as areas with variation in population characteristics. Further, we will recruit clients who are on a variety of THD schedules and ensure that we have representation based on gender, race, and ethnicity. OTPs will assist with recruiting clients by posting and handing out flyers with study information.

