We will employ GLMM models commonly used in the analysis of stepped-wedge trials. ^[[220]](#endnote-220)^, ^[[221]](#endnote-221)^ The models will take the form: 𝐹(𝜇 )=𝜇+𝛽 +𝛿𝑋 +𝛼 +𝜙 ,𝛼~𝑁(0,𝜏2),𝛾 ~𝑁(0,𝜏2) where 𝛽 is a fixed effect for time, 𝑋 is an indicator for intervention in clinic i at time j (coded 0 for the control condition, then 1 from when intervention begins in the clinic through end of study), and 𝛿 is the treatment effect. The models have random effects for clustering at the clinic and individual patient levels, which are assumed to be normally distributed with mean zero and variances 𝜏2 and 𝜏2 , respectively. We will estimate the 𝛼𝜙 effect of intervention while controlling for secular trends and adjusting for clustering within clinic (𝛼𝑖) and individual (𝜙𝑖𝑘), using mixed effects modeling with binary distribution and logit link. Models will be fit using the *glmmTMB* package using R software.^[[222]](#endnote-222)^, ^[[223]](#endnote-223)^ In the case of H1, the primary outcome will be weekly or greater THD, and the fixed-effects coefficients for the intervention effect, exponentiated, will indicate how the intervention increases the odds of weekly or greater THD. Similar mixed models will consider other THD frequencies as outcomes (i.e., 14-day and 28-day). In the case of H3, the same mixed logistic regression model will be used with any adverse events as the outcome, but a one-side test of non-inferiority (i.e., adverse events are no worse under intervention than under the control condition) will be used.^[[224]](#endnote-224)^ We will use a non-inferiority margin of OR≈1.13, which corresponds to an increase in the prevalence of adverse events from 0.20 under the control condition to 0.22 under intervention. In other words, we will test whether the intervention effect is less than OR≈1.13 in a one-sided test. This is equivalent to obtaining a 95% confidence interval for the intervention odds ratio where the upper limit is less than 1.13.

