#### Further Exploratory Analyses

Should we find significant treatment effects of the OTP intervention, we will conduct a series of analyses to develop further evidence that bolsters the inference that the effect is due to the treatment.^[[229]](#endnote-229)^, ^[[230]](#endnote-230)^, ^[[231]](#endnote-231)^ We borrow from methods used in mechanism of treatment research that test whether postulated factors associated with the treatment are also related to the outcome.^[[232]](#endnote-232)^, ^[[233]](#endnote-233)^, ^[[234]](#endnote-234)^ We will test the association between putative mediators and outcomes. For example, the putative mechanism for the OTP intervention is that increased THD will improve retention in care. We will examine the association between THD and retention in care as mediators of the intervention effect. We will also see whether the intervention effect is moderated by characteristics of the population or regional variations. For example, we will also examine variation in intervention impact by region and gender. Any significant moderator effects (e.g., differences in effect size by gender) will suggest that there may be other factors that may account for some of the observed intervention effect. We will also explore variation in effect of the intervention by providers to see if there are moderating effects that suggest variation in treatment implementation. Finally, we will test whether there are lagged treatment effects by introducing interaction terms between treatment and time since intervention start by cohort.^[[235]](#endnote-235)^, ^[[236]](#endnote-236)^ These findings will inform our qualitative study methods. We view these analyses as exploratory since we do not have strong hypotheses regarding the nature of these associations, yet we will use these findings to refine further our interpretation of results and presentation of study findings.

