## Statistical Power

To estimate power for select outcomes, we used a combination of PASS 2022 and Monte Carlo simulation.^[[241]](#endnote-241)^ Using administrative data to estimate sample sizes and baseline rates (μ), we compute detectable differences for 80% power, α = 0.01, ICC=0.05, and SW-RCT with 6 crossover points, and 6 clinics randomized to start at each crossover point. For 7-day or greater THD (i.e., picking up doses every 7 days or less often), we assume the currently prevalence is 0.45. With 36 clinics and approximately 350 clients observed in each clinic in each six-month period (n≈88,200 total observations), power is 93% to detect a small increase (OR=1.1) in the odds of 7-day or greater THD. This corresponds to an increase from a prevalence of 0.45 under the control condition to .47 after intervention. Even when considering racial/ethnic patient subgroups making up just 10% of clinic clients (n≈35 per site and period), power is 86% to detect a modest increase in the odds of 7-day or greater THD (OR=1.3; an increase from 0.45 to 0.52). To estimate power for non-inferiority on the adverse events outcome, we simulated five thousand datasets from a mixed-effects

logistic regression model with the planned stepped-wedge design with no intervention effect. For each of these simulated datasets, the 95% confidence interval for the intervention effect was estimated. Across the five thousand datasets, the upper limit of the odds ratio was less than 1.13 in 4555 datasets, indicating approximately 91% power for the non-inferiority test. Because power is sufficient to detect small intervention effects for the binary outcomes of 7-day or greater THD and adverse events, it is also sufficient to detect small intervention effects on retention in care.

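### The exposure indicator is not tied to the randomised step, so a clinic that never starts could be analysed as a self-selected control

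*Protocol*

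**What the plan says.** What is randomised is the step. Section 5.5 has "Before the trial begins, clinics will be randomized into 6 cohorts", and section 6.1.2 has "OTPs will be randomized across 6 sequential steps between years 2 and 4" and "Six clinics in each cohort will receive the intervention for six months".

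Section 8.2.1 then defines the exposure variable of the mixed model as "coded 0 for the control condition, then 1 from when intervention begins in the clinic through end of study". The coefficient of this variable is the treatment effect for H1 and H3, and H2 uses a clinic-level, time-varying intervention variable in the survival model.

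Two other places describe the start by step. Section 8.3 has "6 clinics randomized to start at each crossover point", and the exploratory analyses refer to "interaction terms between treatment and time since intervention start by cohort".

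Clinic withdrawal is foreseen in sections 5 and 5.4: "If a clinic is considering withdrawing from the study, the Project Manager will schedule an in-person/online meeting". The protocol gives no rule for coding a clinic that starts late or leaves before starting, and it does not state analysis by randomised step.

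**The concern.** The trigger for X is an event in the individual clinic, whereas the randomised quantity is a calendar step. The two coincide only if every clinic starts on schedule.

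All 36 clinics are recruited at the beginning of Year 2. With six-month cohorts, the sixth starts about 2.5 years after the first (5 × 6 months). The clinics are drawn from those ranked low on take-home dosing. A clinic that withdraws while waiting would still appear in the administrative data. If X follows the literal wording, that clinic is 0 throughout. It then supplies control observations after its assigned crossover, including in the final period, when every clinic should have crossed over. Those controls are selected by the clinic's own behaviour. If that behaviour goes with a slower rise in take-home dosing, part of the difference in trend is credited to the intervention.

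**Working it through.** **Reproducing the plan's power.** Inputs from section 8.3: 36 clinics, 6 steps of 6 clinics, 350 clients per clinic and period, ICC 0.05, α = 0.01 (taken as two-sided), control prevalence 0.45, OR 1.1. The total of 88,200 observations implies 88,200 / (36 × 350) = 7 periods.

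For a cross-sectional stepped wedge (Hussey and Hughes):

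Var = Iσ²(σ² + Tτ²) / [(IU − W)σ² + (U² + ITU − TW − IV)τ²]

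- U = 6 × 21 = 126; W = 36 × 91 = 3,276; V = 6 × 91 = 546.
- IU − W = 1,260, and U² + ITU − TW − IV = 5,040.
- OR 1.1 takes 0.45 to 0.4737, a difference of 0.0237. At the mean prevalence of 0.462, τ² = 0.05 × 0.2485 = 0.01243 and σ² = 0.95 × 0.2485 / 350 = 0.000675.
- SE = 0.00579; power = Φ(0.0237 / 0.00579 − 2.576) = 93.5%, against 93% stated. The subgroup figure gives 85.8%, against 86% stated.

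This calculation assumes that every clinic starts at its step. The two codings of X are then identical.

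**Effect of the coding under no true effect.** The check is a GLS fit to clinic-period log-odds (36 × 7, period effects, clinic random effect, m = 350, p = 0.45, ICC 0.05), averaged over random choices of the affected clinics. The model SE of the log OR is 0.024. The number of affected clinics and the slope gaps are assumptions, since the protocol gives neither. The gap is how much less the affected clinics' log-odds rise per half-year.

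| Scenario | Actual-start coding, OR | Randomised-step coding, OR |
|---|---|---|
| 3 never start, no difference | 1.00 | 1.00 |
| 3 never start, stable level 0.5 lower | 1.002 | 1.00 |
| 3 never start, stable level 1.0 lower | 1.004 | 1.00 |
| 3 never start, gap 0.02 | 1.013 | 1.00 |
| 3 never start, gap 0.05 | 1.032 | 1.00 |
| 3 never start, gap 0.10 | 1.066 | 1.00 |
| 6 start one period late, gap 0.02 | 1.003 | 1.00 |
| 6 start one period late, gap 0.05 | 1.006 | 1.00 |
| 6 start one period late, gap 0.10 | 1.012 | 1.00 |

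As a share of the target log OR (ln 1.1 = 0.0953), the three never-start gaps give ln 1.013 / 0.0953 = 14%, ln 1.032 / 0.0953 = 33% and ln 1.066 / 0.0953 = 67%. At α = 0.01 the false-positive rate is about 10 to 11% at a gap of 0.05 and about 54 to 57% at 0.10, against 1 to 2% under step coding. With 2 to 6 never-starters and gaps of 0.02 to 0.05, actual-start coding gives ORs of about 1.009 to 1.058.

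**Cost of step coding.** If the true OR is 1.10 and 2, 4 or 6 clinics never start, for reasons unrelated to trend, step coding gives mean ORs of about 1.095, 1.088 and 1.083. Actual-start coding stays at about 1.10. For H3 with a true OR at the margin of 1.13, step coding with 2, 4 or 6 such clinics gives about 1.123, 1.114 and 1.108. The estimate therefore moves in the direction that makes non-inferiority easier to claim.

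**The case against.** The strongest reply is that the sentence is simply the usual stepped-wedge indicator. Sections 8.3 and 6.1.2 and the exploratory analyses all treat the start as belonging to the cohort, and nothing in the protocol provides for a start date chosen by the clinic. This stands as a reading of intent: the sponsor may already mean the randomised step. It does not remove the point, because section 8.2.1 is where X is defined, and its words refer to the clinic and not to the step.

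A second reply is that handling of withdrawn clinics belongs in the analysis plan, which is not shown and may settle it. That is fair for a rule left unwritten. Here the protocol gives a coding rule, and that rule can be followed to the wrong result.

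Third, the size depends on assumptions. A gap of 0.10 per half-year accumulates to 6 × 0.10 = 0.6 log-odds by the seventh period, roughly 0.45 against 0.31 in prevalence, so it is an upper case. Section 6.1.2 also reports good clinic retention in a similar trial. Both remarks stand, and they are why the result is given as a range.

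A reader might infer that the plan breaks randomisation, that low-capacity clinics bias the result merely by being different, or that any withdrawal turns a clinic into a control. The documents support none of these. The codings agree if clinics start on time, the clinic effect takes up stable differences, and a clinic that starts and then withdraws remains coded 1 to the end of study.

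**Conclusion.** The point holds as an ambiguity in the definition of the primary exposure variable. Its literal reading leaves the randomised comparison unprotected. Late starts of one period are a minor matter. The risk lies with clinics that never start and whose outcome trend differs from the rest. Under the assumptions of 3 such clinics in 36 and a gap of 0.02 to 0.10 log-odds per half-year, a null effect would be reported as an OR of about 1.01 to 1.07, or about one seventh to two thirds of the log OR that the trial is sized for. With no trend difference the bias is nil or negligible.

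For H3 neither coding is safe alone. Step coding dilutes towards non-inferiority. Actual-start coding can err in either direction, because the fit is linear in the log-odds and reversing the sign of the gap inverts the OR.

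**What to change.** In section 8.2.1, state that in the primary analysis X is 1 from the clinic's randomised crossover date to the end of study, whatever its actual start, completion or withdrawal, and that the administrative data of all 36 clinics are kept. Apply the same definition to the intervention variable in the H2 survival model. Name actual-start coding as a sensitivity analysis.

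For H3, report both codings side by side and require the non-inferiority conclusion to be consistent under both.

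The cost is a few lines of text and some dilution if clinics do not start: from OR 1.10 to about 1.083 with 6 of 36 never starting. The 93% power stated in section 8.3 does not change if all clinics start on schedule.

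### The outcome models omit a clinic-by-period random effect, so any clinic-specific drift would make standard errors too small, and the 93% power figure assumes no such drift

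*Protocol*

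**What the plan says.** Section 8.2.1 writes out the mixed logistic model for H1 and applies the same model to H3. Its time term "is a fixed effect for time", shared by all clinics. The random part is stated in words: "The models have random effects for clustering at the clinic and individual patient levels, which are assumed to be normally distributed". The effect is estimated while "adjusting for clustering within clinic (𝛼𝑖) and individual (𝜙𝑖𝑘), using mixed effects modeling with binary distribution and logit link". Neither random effect carries a period index. The discrete-time survival model for H2 also has random effects for patient and clinic only.

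The displayed formula, as extracted, also lists a normal variable gamma that does not appear in the linear predictor and is never defined. The prose names only clinic and patient, so gamma cannot be read as a clinic-by-period term.

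Section 8.3 bases power on "80% power, α = 0.01, ICC=0.05, and SW-RCT with 6 crossover points, and 6 clinics randomized to start at each crossover point". On size it says: "With 36 clinics and approximately 350 clients observed in each clinic in each six-month period (n≈88,200 total observations". On the control rate: "we assume the currently prevalence is 0.45". It concludes that "power is 93% to detect a small increase (OR=1.1) in the odds of 7-day or greater THD", and gives 86% for a subgroup of about 35 clients per clinic and period at OR 1.3. No second correlation parameter is given.

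**The concern.** A constant clinic intercept says that two clients of one clinic are as alike when observed three years apart as in the same half-year. The protocol's own account gives reason to doubt this. Medical directors and nursing staff hold the dosing decisions, uptake of the relaxed rules varied widely between clinics, and billing incentives and regulatory interpretation affect take-home dosing. A change in one clinic's leadership or billing would shift all its clients together from that period on. A patient intercept does not absorb such a shift, because it is constant over periods.

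A stepped-wedge estimate relies heavily on comparisons within a clinic over time. With about 350 clients per clinic-period the binomial noise is very small, so even a little clinic-by-period variance can matter. H1 p-values and the H3 upper confidence limit both come from this model. For H3 the consequence is a finding of no worse safety that is reached too easily.

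**Working it through.** **Inputs, all from Section 8.3.** I = 36 clinics in 6 sequences of 6; m = 350; control prevalence 0.45; ICC 0.05; alpha 0.01 (sidedness not stated). Periods: T = 88,200/(36 × 350) = 7, or 3.5 years. OR 1.1 moves 0.45 to 0.4737, so d = 0.0237.

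**Assumption.** CAC is not in the protocol. A range from 1.00 to 0.80 is used, with the within-period ICC held at 0.05.

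**Variance components (risk-difference scale).**
- Total: 0.45 × 0.55 = 0.2475.
- Clinic: 0.05 × 0.2475 = 0.012375.
- Binomial part of a clinic-period mean: 0.95 × 0.2475/350 = 0.000672.
- Clinic-by-period part: 0.012375 × (1 − CAC). At CAC 0.95 this is 0.000619, nearly as large as the binomial part.

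**Formula (Hussey-Hughes).** Let a = 0.000672 + 0.012375(1 − CAC) and t = 0.012375 × CAC.

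Var = I·a(a + T·t) / {(I·U − W)a + (U² + I·T·U − T·W − I·Q)t}

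U = 126 is the number of treated clinic-periods. W = 3,276 sums the squared period totals of treated clinics. Q = 546 sums the squared clinic totals of treated periods. The two brackets are 4,536 − 3,276 = 1,260 and 15,876 + 31,752 − 22,932 − 19,656 = 5,040.

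**The protocol's figure (CAC = 1).** The numerator is 36 × 0.000672 × 0.08730 = 0.002111. The denominator is 1,260 × 0.000672 + 5,040 × 0.012375 = 63.22. SE = 0.00578 and d/SE = 4.10. Power = Φ(4.10 − 2.576) = 93.6%, against a stated 93%. With m = 35 and OR 1.3 the same method gives 86.2%, against a stated 86%. Other reasonable variance choices give 92.1-93.6% and 83.7-86.2%. One-sided 0.01 gives 95-96% and two-sided 0.05 gives 98%, so neither matches the 93%.

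**With clinic-by-period variance.** At CAC 0.95, a = 0.001291 and t = 0.011756, so SE = 0.00799, d/SE = 2.97 and power = 65%. For error rates, the planned model still reports SE ≈ 0.00578. The true SE of the same estimator comes from its sandwich variance, and their ratio is r. Two-sided type I error is 2Φ(−2.576/r). The one-sided non-inferiority error is Φ(−1.96/r).

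| CAC | Power, OR 1.1, term added | Power, OR 1.3 subgroup (m = 35) | r | Type I error, nominal 1% | Non-inferiority error, nominal 2.5% |
|---|---|---|---|---|---|
| 1.00 | 93.6% | 86% | 1.00 | 1.0% | 2.5% |
| 0.99 | 88% | 85% | 1.09 | 1.8% | 3.6% |
| 0.98 | 82% | 85% | 1.17 | 2.7% | 4.7% |
| 0.95 | 65% | 83% | 1.38 | 6.2% | 7.8% |
| 0.90 | 45% | 79% | 1.68 | 12.5% | 12.2% |
| 0.80 | 26% | 73% | 2.15 | 23% | 18% |

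Power for OR 1.1 drops below 80% once CAC is under about 0.976. The last column assumes that adverse events share the ICC of 0.05 and the CAC. Given those, r does not depend on prevalence.

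**Simulation check.** Logit-scale data were generated with no effect, 1,000 trials per setting, and analysed with a clinic intercept only. Rejection at nominal 1% was 1.5% at CAC 1, 1.3% at 0.98, 4.5% at 0.95 and 8.2% at 0.90. At CAC 0.95 the empirical SD was 0.031 against a mean model SE of 0.024. The excess is confirmed at 0.95 and 0.90, somewhat smaller than the formula gives. At 0.98 it cannot be told apart from the CAC 1 result at the 1% level, so the figures for CAC 0.98 and 0.99 rest on the formula alone.

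**The case against.** A reader might infer that the planned intervals are too narrow as a matter of fact. The documents do not support that. They give no CAC and no estimate of clinic drift, so the understatement is conditional on clinic-by-period variance above zero.

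A reader might also infer that 93% power is available only if clinics never drift apart. That describes the protocol's calculation as reproduced here, but not every form of the design. Clients are followed over time and the model has a patient effect. In an illustrative closed cohort with half the within-clinic variance at patient level, power exceeds 99% at CAC 1, stays at 93% down to a CAC of about 0.97, and is 81% at 0.95 and 55% at 0.90. That cushion stands for power. It does nothing for type I error.

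Other points also stand:
- The subgroup power falls only modestly.
- The practical loss at alpha 0.01 is bounded. The OR detectable with 80% power is 1.08 at CAC 1, 1.12 at 0.95, 1.14 at 0.90 and 1.19 at 0.80, all below the OR of 1.3 that Section 8.3 treats as modest.
- The drift argument is about take-home dosing policy. Its extension to emergency visits, hospitalizations and deaths is an assumption.

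It can be said that Section 8.2.1 allows analyses to grow as complex as the hypotheses require, and that the exploratory section examines provider variation and lagged effects. Neither repairs the primary standard error. The first names no term, and the exploratory work follows only a significant result. Nor is this detail left to an analysis plan, since the protocol itself writes out the random effects and the power.

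**Conclusion.** The concern holds in conditional form. The H1, H2 and H3 models make no allowance for clinic-specific change over seven periods, and the stated 93% and 86% correspond closely to a calculation with no such change.

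If CAC is below 1, the H1 test is anti-conservative: about 2% at nominal 1% for CAC 0.99 (formula only), 4.5-6% at 0.95 and 8-13% at 0.90. If adverse events behave alike, the nominal one-sided 2.5% non-inferiority error would be about 4-12% over CAC 0.99 to 0.90. Power for OR 1.1 would be 88%, 65% and 45% at CAC 0.99, 0.95 and 0.90, with clients treated as independent between periods, and higher if clients recur and their correlation is modelled.

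The omission is certain; the size of its effect is not, because it depends on a parameter the protocol does not supply. No size was computed for H2, where the point is structural. The protocol's 91% non-inferiority power is not judged here.

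**What to change.** Add a clinic-by-period random intercept (nested exchangeable structure) to the H1, H2 and H3 models, and specify a discrete-time decay correlation as a sensitivity analysis. Define or remove gamma in the displayed formula. Restate Section 8.3 power over a CAC range such as 0.8 to 1.0, using a CAC estimated from the State's existing pre-trial clinic data, and state how repeated clients enter the calculation.

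The cost is one further random term in the planned software and a revised power statement, with no change to trial conduct. The downside is wider intervals and a less favourable power figure. If the estimated CAC is very close to 1, little is lost.

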For the retention outcome (H2), a multilevel discrete-time survival model will be used.^[[225]](#endnote-225)^, ^[[226]](#endnote-226)^, ^[[227]](#endnote-227)^An expanded person-period dataset will be constructed.^[[228]](#endnote-228)^ The outcome will have two possible states in any time period: 0 = retained in treatment; 1 = treatment exit. The multilevel analysis approach can accommodate recurring events for the same individual, with individuals leaving the set of patients “at risk” for dropout until treatment is initiated again. Analysis of the person-period dataset will use a mixed-effects regression model with a complementary log-log link function and random effects for patient and clinic. With the complementary log-log link, the coefficients can be interpreted as the relative effect on the hazard of event occurrence. Discrete time intervals in which an individual may be retained or not retained will be one month in length, and a set of dummy variables will capture differences in risk of dropout across these intervals. Time will be relative to the initiation of treatment, which may have been many months before the start of the study for some patients. In a sensitivity analysis, we will restrict the retention outcome to patients who have been in treatment for less than 12 months at the start of the study. The discrete-time multilevel model accommodates both time-invariant patient characteristics as well as time-varying patient and clinic characteristics as explanatory variables. Our focus will be on the time-varying intervention condition variable at the clinic-level, adjusting for patient characteristics such as demographics and prior treatment experience. Intervention effects will be visualized by plotting fitted hazard of dropout against month since treatment initiation separately for control and intervention observations. The multilevel discrete-time survival model can be used for other time to event outcomes such as time to all- cause mortality.

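### The retention (H2) model adjusts for time in treatment but states no calendar-period term, so a shared trend in dropout enters the intervention effect

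*Protocol*

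**What the plan says.** Section 8.2.1 describes two models.

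- **H1 and H3 (take-home dosing, adverse events).** A mixed model with logit link, in which one term "is a fixed effect for time". The stated purpose is to estimate the "effect of intervention while controlling for secular trends and adjusting for clustering within clinic". The text assigns this model to H1 and then, as the same logistic model, to H3.
- **H2 (retention).** A separate paragraph begins: "For the retention outcome (H2), a multilevel discrete-time survival model will be used". It is a "mixed-effects regression model with a complementary log-log link function and random effects for patient and clinic". The intervals are months, and the time origin is explicit: "a set of dummy variables will capture differences in risk of dropout across these intervals. Time will be relative to the initiation of treatment". For some clients that origin may lie well before the study began. The covariates are described as follows: "Our focus will be on the time-varying intervention condition variable at the clinic-level, adjusting for patient characteristics such as demographics and prior treatment experience".

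The planned H2 plots show fitted dropout hazard by month since treatment start, separately for control and intervention observations. The same paragraph offers this model for other time-to-event outcomes, including all-cause mortality. Section 8.2.3 reuses it for the race/ethnicity interactions.

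**The concern.** Once a clinic starts the intervention it is coded as exposed to the end of the study, so exposure rises with calendar time by design. Calendar time is therefore the main confounder in a stepped wedge. The H1/H3 model deals with it. The H2 paragraph sets out link, random effects, time axis and covariates, but the only time it adjusts for is the client's own. Following that paragraph would make H2 largely a before-after comparison within clinics.

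A trend is plausible on the protocol's own account. Section 2.2 says the State has introduced bundled payments and will keep its waiver and continue to encourage take-home dosing outside the trial. The protocol expects more take-home dosing to improve retention. If dosing practice loosens statewide, dropout would fall in control and intervention clinics alike, and the H2 model would credit the fall to the intervention. A trend in the other direction would hide a real benefit. H2 is one of the three hypotheses under Aim 4.

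**Working it through.** **Inputs from the protocol.** Section 8.3 gives 36 clinics, six starting at each of 6 crossover points (hence 7 six-month periods), about 350 clients per clinic and period, α = 0.01 and ICC = 0.05. The total agrees: 36 × 7 × 350 = 88,200.

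**The plan's own figure.** Section 8.3 calculates no power for H2; it infers it from the binary outcomes. The H1 figure can be checked with the Hussey-Hughes variance, which includes fixed period effects and a random clinic effect:

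Var = Iσ²(σ² + Tτ²) / [(IU − W)σ² + (U² + ITU − TW − IV)τ²]

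Here I = 36, T = 7, U = 126, W = 3,276, V = 546, σ² = 0.45 × 0.55/350 and τ² = (0.05/0.95) × 0.45 × 0.55. The SE is 0.00593. An OR of 1.1 takes 0.45 to 0.4737, so power = Φ(0.0237/0.00593 − 2.576) = 92.2%, against 93% stated. The 10% subgroup gives 84.0%, against 86% stated. The stated H1 power is therefore in line with an analysis that carries period effects.

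**Calendar separation within a clinic.** Sequence s (1 to 6) is control in periods 1 to s, with mean (s + 1)/2, and intervention in periods s + 1 to 7, with mean (s + 8)/2. The difference is 3.5 periods, or 21 months, in every sequence.

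**Expected bias.** If the dropout hazard is multiplied by g each period in all clinics and the intervention does nothing, a model without period terms should return HR ≈ g^3.5.

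**Check by fitting.** Expected person-month data were built for the planned layout: 42 months and an open cohort of 350 clients per clinic. These values were assumed:

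- monthly exit hazard of 8% in the first three months, then 6%, 4%, 2.5% and finally 1.2% beyond 24 months;
- clinic SD of 0.3 on the log-hazard scale;
- true HR of 1.

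The fit was a complementary log-log regression with tenure-band dummies. Clinic dummies replaced the clinic random effect, and the patient random effect was left out. With b the fitted log HR and s its SE, the false-positive rate is 1 − Φ(z − b/s) + Φ(−z − b/s).

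| Dropout trend per period | g^3.5 | HR, no period terms | False positive, two-sided 5% | False positive, two-sided 1% | HR with period terms |
|---|---|---|---|---|---|
| 1% fall | 0.965 | 0.966 | 39% | 19% | 1.000 |
| 2% fall | 0.932 | 0.932 | 91% | 77% | 1.000 |
| 3% fall | 0.899 | 0.899 | 99.8% | 99% | 1.000 |
| 5% fall | 0.836 | 0.837 | about 100% | about 100% | 1.000 |
| 2% rise | 1.072 | 1.071 | 94% | 83% | 1.000 |
| 5% rise | 1.186 | 1.185 | about 100% | about 100% | 1.000 |

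For the 2% fall, b = ln 0.932 = −0.070 and s = 0.0212, so b/s = −3.32 and the rate is Φ(3.32 − 1.96) = 91%. A refit with monthly tenure dummies gives the same HRs for the 2% and 5% falls (0.932 and 0.837).

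**On an annual scale.** A fall of 5% per year gives 0.95^(21/12) = 0.914, and 10% per year gives 0.90^(21/12) = 0.832. Direct fits without period terms return the same values.

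**With a real benefit.** If the true HR is 0.90, a 2% rise per period gives 0.964 and a 5% rise gives 1.066, so the sign reverses. With period terms both return 0.900.

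**Precision.** With no trend, the SE of the log HR goes from 0.0204 to 0.0309 when period terms are added. The variance ratio is (0.0309/0.0204)² = 2.3.

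**The case against.** The best counter-reading is that the general form already covers H2. Section 8.2.1 is headed as covering all three outcomes, opens with mixed models for stepped-wedge designs, and writes its model with a generic link and a time effect. The H2 model could be that form with a complementary log-log link, the tenure dummies being the baseline hazard that any discrete-time model needs. The covariate list is also open-ended, and the model is said to accommodate time-varying clinic characteristics.

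That reading is possible, but the text does not commit to it. The sentence on secular trends is tied to the logit link, the outcomes assigned to that model are H1 and H3, and the H2 paragraph then redefines time as tenure. Saying that a model can hold time-varying covariates does not commit to a calendar term. Nor is this simply left to an analysis plan: the protocol itself fixes the H2 time axis.

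Several narrower points stand:

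- About 3.5 of the 6 period steps of trend pass into the estimate, not the whole trend, and only to the extent that clinics share it.
- With a clinic random effect, between-clinic contrasts contribute a little, so H2 is not purely before-after.
- Weekly or greater take-home dosing (H1) is the only outcome Section 8.2.1 calls primary.
- The sensitivity analysis in clients with under 12 months of treatment at study start would be largely protected if it is a closed cohort, because tenure and calendar time then nearly coincide. A 5% fall per period gives HR 0.976, but with an SE of about 0.09. If later entrants are included the protection goes (HR 0.840).
- A closed cohort of all clients present at the start is little better than the open one (HR 0.852).

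The exploratory lag analysis in Section 8.2.1 does not help. It uses time since intervention start and is run only after a significant effect.

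**Conclusion.** The concern holds. As written, the H2 model states no adjustment for calendar time, and in this layout about 3.5 periods' worth of any common trend in dropout would be reported as intervention effect. A fall of only 1% to 2% per six months would produce HRs of 0.966 to 0.932 from an intervention that does nothing, with false-positive rates of 39% to 91% at a nominal two-sided 5%. The 21-month separation follows from the design alone. The size of the bias depends on the trend, and the protocol gives neither a retention rate nor a trend, so the trends and hazards above are assumptions. This should be corrected before H2 is analysed, because it can create or reverse the result of a named hypothesis.

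**What to change.** In the H2 paragraph of Section 8.2.1, state that the discrete-time model includes fixed effects for calendar period (month or six-month step) in addition to the dummies for month since treatment initiation. Carry the same term into the race/ethnicity version (Section 8.2.3) and into any mortality analysis that uses this model. Base the fitted-hazard plots on the period-adjusted model. In Section 8.3, replace the inference about retention power with a calculation that includes the period term.

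The change costs about one sentence per place and needs no new data. The SE of the log HR rises by about half (0.020 to 0.031 under the assumptions above). That is the precision the design actually offers once calendar time is controlled.
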